#### Follow-up procedure

Eight weeks after the end of treatment, the PSQI, fMRI, HAMD, HAMA, PSG, and sleep diary records will be collected.

### Outcome

#### Primary outcome

Our primary outcome will be the mean change scores of insomnia severity assessed using PSQI from baseline to the end of the treatment period. The PSQI is a 19-item insomnia assessment tool consisting of seven component scores, including sleep quality, sleep latency, sleep duration, sleep efficiency, sleep disorders, hypnotic medication, and daytime dysfunction. The higher score reflects the worse sleep quality.

#### Secondary outcomes

The secondary outcome in this study will be mean change scores of HAMD and HAMA, the weekly average of the components in the sleep diaries during the 1-week period, and changes of the sleep latency (SL), sleep efficiency (SE), total sleep time (TST), and so on which are collected through PSG between the baseline, post-treatment assessment, and 8-week follow-up.

##### Sleep diary

The sleep diary will be kept by the ID patients to record their sleeping and waking times as well as additional sleep-related factors. It is a useful tool to assess sleep quality and monitor whether treatment is working.

##### HAMD and HAMA

The HAMD and HAMA will be used to assess depression and anxiety of ID patients. In this study, we will adopt the 17-item scale of HAMD and the 14-item scale of HAMA. The HAMD and HAMA score of more than 7 points are considered as may be present depressive and anxiety symptoms.

##### PSG

We will use PSG to collect sleep parameters (TST, sleep latency, actual total sleep time, sleep efficiency) and sleep stage (N1, N2, N3, REM sleep, percentage of total sleep time in each phase).

#### Safety monitoring

Potential adverse events of mPFC-rTMS include mild headache, memory impairments, and seizures. Participants will be asked to report any adverse events at each patient visit. There is no anticipated harm and no compensation for participants.

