### Participants and recruitment

We will post recruitment information in the hospital to recruit participants who report clinically significant insomnia. Prior to recruitment, the investigator will inform participants of the benefits, as well as possible risks (poor therapeutic effects and adverse events associated with rTMS) in the study. Informed consent will be obtained by investigators. All participants will sign informed consent forms before collecting data and randomization. Investigators will also sign the informed consent forms and record the informed consent process in the medical records.

Investigators will decide whether the participants meet the inclusion criteria based on the scores of PSQI, HAMD, and HAMA. The eligible participants will complete a baseline rs-fMRI, a 1-week sleep diary, and a 1-day polysomnography (PSG). All participants who satisfy the inclusion criteria will be randomly divided into either a real mPFC-rTMS group or a sham mPFC-rTMS group in a ratio of 1:1.

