#### Inclusion criteria

Participants who comply with all the following criteria will be enrolled in the clinical trial:Aged 18–65Meeting the diagnostic criteria for insomnia disorder according to the Diagnostic and Statistical Manual of Mental Disorders, Fifth EditionPSQI score > 11 points, HAMD-14 score < 7, HAMA score < 14, and HAS score > 32Sign informed consent forms for this studyHave not received medications for anxiety, depression, or insomnia within 4 weeks prior to enrollment in the studyNo history of staying up late and shift in the past 4 weeks

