#### Exclusion criteria

Participants who comply with one or more of the following criteria will be excluded from the clinical trial:Having a family history of mental illness or other mental illnessA history of alcohol and drug abuseInsomnia caused by other sleep disorders such as sleep apnea syndrome and restless legs syndromeSerious medical diseases including the cardiovascular system, nervous system, urinary system, respiratory system, digestive system, and other serious physical diseasesPregnant or breastfeeding womenReceived physical therapy such as rTMS, transcranial direct current stimulation, or electroshock in the last monthsContraindication for MRI including claustrophobia, abnormal signal, or obvious asymmetrical head structure by MRI

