### Oversight and dissemination

#### Composition of the coordinating center and trial steering committee

A monitoring/steering/safety committee will not be set up for this study. The study management team will be responsible for the organization of the trial including identifying potential recruits and obtaining informed consent and data collection. The study management team will meet at the beginning, the interim, and the end of the trial to monitor the study regularly to ensure adequate recruitment rate, data accuracy, and data validity.

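### Seizure is a listed risk of the study treatment, but the exclusion list does not clearly keep out a patient with a past seizure

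*Protocol article*

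**What the plan says.** Under Safety monitoring, the protocol article states: "Potential adverse events of mPFC-rTMS include mild headache, memory impairments, and seizures". It adds that participants are asked about adverse events at each visit, and ends: "There is no anticipated harm and no compensation for participants". Under Participants and recruitment, patients are to be told before entry of "possible risks (poor therapeutic effects and adverse events associated with rTMS").

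Entry is governed by two lists. The Inclusion criteria open with "Participants who comply with all the following criteria will be enrolled in the clinical trial", and the Exclusion criteria follow. Three exclusions bear on seizure risk without naming it:

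- serious disease of several organ systems, the nervous system among them
- a history of alcohol and drug abuse
- the MRI contraindication item, whose examples include abnormal signal and marked head asymmetry

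The one exclusion that mentions rTMS concerns recent treatment: "physical therapy such as rTMS, transcranial direct current stimulation, or electroshock in the last" months. Neither list has an item for past seizures, for epilepsy by name, or for contraindications to rTMS.

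**The concern.** The protocol itself lists seizure as a possible effect of the treatment under test. The entry criteria would then be expected to say whether a person who has already had a seizure may receive that treatment. They spell out contraindications for the scan but not for the stimulation.

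What is at stake is the safety of a small group: people with a past seizure, no current serious neurological disease and an unremarkable MRI. Whether such a person is randomised depends on one investigator's reading of one adjective. The other safeguards (questions at visits, stopping and treating after serious events, emergency unblinding) come into play only once treatment has begun. The primary comparison is not affected.

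**Working it through.** No stated figure is in dispute, so the main check sets the criteria against the named risk.

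**1. Does any entry item reach a past seizure?**

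| Item (Inclusion or Exclusion criteria) | Active epilepsy | Past seizure, now well, normal MRI |
|---|---|---|
| Serious disease, nervous system included | Probably excluded | Unclear; turns on the word serious |
| Alcohol and drug abuse | Only if present | Only if present |
| MRI contraindication, including abnormal signal | Only if the scan shows it | Not reached |
| Recent rTMS or similar treatment | Not reached | Not reached |
| No anxiety, depression or insomnia drugs for 4 weeks | Not reached | Not reached |

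The right-hand column has no clear exclusion.

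**2. Exposure, from the Real mPFC-rTMS group section**

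- Pulses per session: 200 repetitions × 5 s × 1 Hz = 1000, which matches the stated total.
- Session length: 200 × (5 s + 1 s) = 1200 s = 20 min, which also matches.
- Sessions per patient: 5 per week × 4 weeks = 20.
- Pulses per patient: 20 × 1000 = 20,000.
- Real-arm sessions: 30 patients × 20 = 600.

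These figures describe dose, not risk. The documents give no seizure rate for 1 Hz at 80% of resting motor threshold, so no expected number of seizures can be derived.

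**3. Cost of an explicit exclusion**

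Let p be the share of otherwise eligible patients with a seizure history. The documents do not give p; the range 0.5% to 5% is an assumption. Extra patients needed to fill 60 places = 60/(1 − p) − 60.

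- p = 0.005: 60/0.995 − 60 = 0.3
- p = 0.05: 60/0.95 − 60 = 3.2

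**4. The harm sentence**

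The same short section lists memory impairments and seizures and then says that no harm is anticipated. The recruitment section treats rTMS adverse events as risks to be disclosed. The wording does not sit well together, but no procedure depends on the sentence.

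**The case against.** The strongest reply is that this is a condensed article. The Trial status section cites a protocol, version 1.1, which is not shown. Quality control and guarantee says researchers are trained in the entry criteria and in rTMS operation. A device safety screen may therefore exist elsewhere. That is possible and limits confidence. However, the article presents its two lists as the criteria that decide entry, and it does spell out contraindications for the scan.

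A second reply is that most of the risk is already covered. This largely stands. Active epilepsy would probably fall under serious nervous-system disease. Drugs for anxiety, depression and insomnia are barred before and during the trial, which narrows any worry about drugs that lower the seizure threshold. What remains is the isolated past seizure.

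A third reply is that potential and anticipated mean different things, and that the harm sentence mainly introduces the statement on compensation. That is fair: it is a wording inconsistency, not a failure of safety procedure.

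Three stronger readings are tempting, and the documents do not support them:

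- *Screening rests on three scales.* A reader might infer this from "Investigators will decide whether the participants meet the inclusion criteria based on the scores of PSQI, HAMD, and HAMA". The sentence concerns inclusion only and cannot be exhaustive, since the Inclusion criteria also require an age range, a DSM-5 diagnosis and a drug-free period. It says nothing about how exclusions are checked.
- *Nobody reviews adverse events.* A reader might infer this because the management team meets "to monitor the study regularly to ensure adequate recruitment rate, data accuracy, and data validity". Silence in a statement of purpose does not show that safety is ignored. The same team is responsible for ongoing management and for supervising the research process.
- *The plan permits patients with a past seizure.* It does not say so. The criteria are ambiguous, and ambiguity is not permission.

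**Conclusion.** The point holds in a limited form. The exclusion list does not clearly address a risk that the protocol names for its own treatment. The gap is confined to patients with a past seizure and no current serious neurological disease. It should be closed because the remaining safeguards act only after exposure begins and closing it costs little.

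Its size cannot be stated as a risk. The exposure is 20,000 pulses per real-arm patient over 20 sessions, and the absolute probability of a seizure may be low. The conclusion rests on reading the published lists as the operative criteria; an rTMS safety screen in the full protocol would reduce the point to a reporting gap. The harm sentence is a minor edit whatever the full protocol says. Confidence is medium.

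**What to change.** In the Exclusion criteria, add: *history of seizure or epilepsy, or other contraindication to rTMS*. Check it with a question at the existing screening visit. The clinical team should write down the other contraindications, so that the item does not bring back the discretion it is meant to remove.

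Recruitment is under way, so this is an amendment that applies to patients screened from then on. It does nothing for anyone already randomised.

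As a minor accompanying edit under Safety monitoring, replace the statement that no harm is anticipated with wording that matches the risks listed there and disclosed before entry.

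The cost is one criterion, one screening question and one sentence, plus about 0 to 3 more screen failures under the assumed 0.5% to 5%. The criterion acts before randomisation, so the 1:1 allocation, the 30 per arm and the comparison of randomised groups stay as planned. No new committee or staff are needed.

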#### Quality control and guarantee

At the begaining of the study, the whole research process, criteria for inclusion and exclusion, rTMS operation, curative effect observation, data collection and management, and adverse event reporting and recording will be trained for the researchers.

The trial will be withdrawn under the following conditions:Patients with deterioration conditionPatients with serious adverse events who need to stop rTMS treatmentOther serious physical diseases during the testFrom the medical and ethical perspective, the researcher considered that it is necessary to terminate the researchParticipants are reluctant to continue the study and withdrawal of informed consent for non-medical reasonsWithdrawal of informed consent

The research data will be recorded and stored correctly, completely, and consistent with the original data in the form of double data entry under the study management team which is set up to take charge of quality control and supervise the research process. The scale evaluation is completed by designated persons. PSG is conducted by professionals in the Sleep Rehabilitation Center of Zhenjiang Mental Health Center. fMRI is conducted by professionals in the Imaging Department of Zhenjiang Mental Health Center. When the subjects drop out, the researchers will interview by face to face, phone, or mail, and so forth to ask for reasons, record the time of the last treatment, and complete the evaluation items as far as possible. Patients with deterioration conditions, adverse events, and other serious physical diseases will be taken corresponding treatment measures. Patients who have been ranked with random numbers will be included in the statistical analysis if they received more than half of the treatment course. All dropouts will be analyzed according to the intention-to-treat principle after the trial.

Patients will be numbered instead of their names. Personal information will be collected through these numbers. Informed consent forms will be secured in a locked cabinet with a special lock and a special person to keep it. Do not allow to discuss the subject’s condition or information publicly in any place in addition to the research center. We will keep patient study records confidential as relevant law which provides guarantees for the security of privacy, data, and authorized access. Any information in the study records such as name, ID number, address, and telephone number that can directly identify the patient will not be disclosed outside the Zhenjiang Mental Health Center unless required by relevant laws.

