### Sample size

This study aims to determine the efficacy and brain mechanism of mPFC-rTMS in ID patients. Based on preliminary experiments, the PSQI score significantly decreased by 4.43 ± 3.60 in the group treated with mPFC-rTMS compared to 1.30 ± 2.58 in the control group. Based on a power analysis, 26 patients per group were required to detect a significant difference (power = 0.9, *α* = 0.05, two-sided). Thus, considering a 15% dropout rate, we plan to recruit 30 patients per group to compensate. As to fMRI research, there is no known sample size calculation. However, for the exploratory study, 15 to 30 patients are adequate to test the null hypothesis [26].

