#### Intervention

The subjects will be prohibited from receiving any other relevant treatments including drugs that can improve sleep during the trial period. *There are concomitant medications such as medications for anxiety, depression, or insomnia that are prohibited during this trial*. All relevant treatments and compliance will be recorded in the case report form. We attempted to improve adherence to interventions by strategies (i) emphasizing to participants the importance of their attendance at follow-up assessments even if they were no longer compliant with the intervention; (ii) during the follow-up period, investigators will be arranged to respond to patient inquiries; (iii) investigators will contact patients 2 (± 1) days before each visit via letters and telephone contact; and (iv) providing training in issues related to compliance for all study investigators who will contact the participants.

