#### Real mPFC-rTMS group (shown in Fig. 2)

All operators who operate mPFC-rTMS will receive training to ensure consistent rTMS technique on all participants. Deep transcranial magnetic stimulation (dTMS) was administered using a Magstim Rapid2 TMS stimulator (Magstim, Whitland, UK) with H7 coil (Brainsway, Jerusalem, Israel). The front rim of the helmet was fixed at 1 cm above the nasion, then the treatment location of the H7 coil stimulates mPFC bilaterally. Before the first treatment session, single-pulse TMS was delivered to measure the resting motor threshold (RMT) of the extensor halusis brevis muscle of the participant’s toes. RMT was defined as the minimum intensity, which elicited 3 motor evoked potential (MEP) responses in 6 attempts. Treatment parameters were 1 Hz, 5-s stimulation, and 1-s stimulation intervals with a stimulation intensity of 80% of RMT. The number of repetitions was 200, the total number of pulses was 1000, and the total stimulation time was 20 min. The real mPFC-rTMS therapy will be performed 1 time per day 5 days per week for 4 weeks.

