### Statistical analysis

For clinical data, statistical analyses will be analyzed using Statistical Package for the Social Sciences (version 19.0). Two-sided tests will be considered statistically significant if *P* ≤ 0.05. Cases of any missing data should be listed and the reasons should be indicated. The main efficacy analyses will be conducted based on the intention-to-treat principle. Sociodemographic information and outcome indicator will be presented with the mean ± standard deviation or the frequency (%) for the real mPFC-rTMS group and the sham mPFC-rTMS group. Independent *t* tests will be used to compare the outcome indicators between the two groups before and after mPFC-rTMS. Paired *t* tests will be used to compare the pre-rTMS and post-rTMS outcome indicators within each group. A repeated measures analysis of variance with adjustments for non-sphericity will be applied to analyze the group differences and time-dependent effects of rTMS on outcome indicators.

For fMRI data, statistical analyses will use SPM12 (http://www.fil.ion.ucl.ac.uk/spm), Data Processing & Analysis of Brain Imaging toolbox (http://rfmri.org/dpabi), and VBM8 toolbox (http://dbm.neuro.unijena.de/vbm) plugged into MATLAB_R2018a (Mathworks, Inc., Natick, MA, USA). Original data will be preprocessed: slice timing, affine head motion, nonbrain extraction, spatial smoothing, and temporal filtering will be applied. The regional resting-state fMRI time series will extract for the bilateral mPFC by using the average functional time series of all voxels within each region. Significance was set at a *P* value < 0.05 after correcting for multiple comparisons using false discovery rate (FDR) correction. Pearson correlation will be used to investigate the RSFC between bilateral mPFC and the whole-brain regions, and then a Fisher’s *r*-to-*z* transform is employed. mPFC-based functional connectivity pre-rTMS and post-rTMS between the real and sham mPFC-rTMS group will be compared using independent *t* tests. Paired *t* tests will be used to compare pre-rTMS and post-rTMS mPFC-seed functional connectivity within each group.

There will be no interim analysis.

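### Inclusion in the analysis is made conditional on more than half of the treatment course, with no per-protocol label, which contradicts the intention-to-treat analysis stated elsewhere

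*Protocol article*

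**What the plan says.** Three statements in the protocol article decide who is analysed.

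- **Quality control and guarantee, inclusion condition.** "Patients who have been ranked with random numbers" are to enter the analysis on a condition: they "will be included in the statistical analysis if they received more than half of the treatment course". The condition applies to people who have already been allocated.
- **Quality control and guarantee, next sentence.** "All dropouts will be analyzed according to the intention-to-treat principle after the trial".
- **Statistical analysis.** "The main efficacy analyses will be conducted based on the intention-to-treat principle".

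Three further places bear on the point.

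- Treatment is given "1 time per day 5 days per week for 4 weeks" (Real mPFC-rTMS group), which makes 20 sessions.
- The reasons for withdrawal listed under Quality control and guarantee include deterioration, serious adverse events that stop rTMS, and withdrawal of consent for non-medical reasons.
- The trial means to keep assessing people who stop. The Intervention section stresses to participants the importance of "their attendance at follow-up assessments even if they were no longer compliant with the intervention", and Quality control and guarantee asks staff to "complete the evaluation items as far as possible" after dropout.

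**The concern.** A condition based on the amount of treatment received is a compliance criterion applied after randomisation. It cannot govern the same analysis as intention-to-treat. The article mentions no per-protocol or sensitivity analysis to which the condition could belong; it is attached simply to the statistical analysis.

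Two things are at stake.

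- **If the condition is applied to the primary PSQI comparison,** patients who stop early leave the analysis. Some will have stopped because they were getting worse or had a serious adverse event. If that happens differently in the two arms, the comparison no longer rests on randomisation alone.
- **If it is left unresolved,** two analysis sets are both defensible from the text, and the choice between them could be made after the data are seen. In a trial of 60 patients, a few exclusions can matter.

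This is a conflict between stated sentences. It is not a detail left to a fuller document.

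**Working it through.** **1. The sentences set against one case.** The course is 5 × 4 = 20 sessions, so more than half means at least 11. Take a randomised patient who stops at session 8.

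| Statement | Is the patient analysed? |
|---|---|
| More-than-half condition | Does not qualify |
| All dropouts by intention-to-treat | Yes |
| Main efficacy analyses by intention-to-treat | Yes |

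The three cannot all hold for the same analysis.

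**2. The plan's own figures.** The Sample size section reports that "the PSQI score significantly decreased by 4.43 ± 3.60 in the group treated with mPFC-rTMS compared to 1.30 ± 2.58 in the control group". The difference is 4.43 − 1.30 = 3.13, and the pooled SD is √((3.60² + 2.58²)/2) = 3.13. The usual formula, n = 2(1.960 + 1.282)² × (SD/difference)², gives 22 per group at 90% power (23 with the t distribution), against the stated 26. The stated figure is not reproduced but is on the cautious side. Nothing below depends on it; only the SD of 3.13 and the 30 per arm are carried forward.

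**3. What the condition could do if applied.** The documents do not give the number stopping by session 10, the split between arms, or how stopping relates to PSQI change. These are therefore assumptions. Simulation with 40,000 trials per scenario:

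- 30 per arm, normal change scores with SD 3.13, no true effect.
- In each arm, the k patients ranked lowest on a latent variable are removed. That variable has the stated correlation with PSQI improvement, and 0 means removal at random.
- A pooled two-sided t test at 0.05 is run on those left.
- Positive bias favours real rTMS.

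| Removed per arm | Correlation, real arm | Correlation, sham arm | Bias (PSQI points) | Type I error |
|---|---|---|---|---|
| 1 | 0.5 | 0 | 0.11 | about 5.5% |
| 2 | 0.5 | 0 | 0.21 | about 6% |
| 4 | 0.3 | 0 | 0.22 | about 6% |
| 4 | 0.5 | 0 | about 0.37 | about 7% |
| 4 | 1.0 | 0 | about 0.75 | about 17% |
| 4 | 0 | 0 | 0 | 5% |
| 4 | 0.5 | 0.5 | 0 | just under 6% |
| 4 | 0 | 0.5 | about −0.37 | about 7.5% |

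Bias in the real-arm-only rows is proportional to the correlation: 0.75 × 0.5 = 0.375 and 0.75 × 0.3 = 0.225, which agrees with the table. Four per arm is 4/30 = 13%, close to the whole 15% dropout allowance. A correlation of 1.0 means that exactly the worst responders are removed, so that row is a bound and not an expectation.

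**4. What full intention-to-treat costs in power.** With all 30 per arm analysed, the planned effect and SD 3.13, t-test power is 0.968. Suppose 5%, 10% or 15% of the real arm show only the sham-level change. The difference becomes 3.13 × 0.95 = 2.97, 3.13 × 0.90 = 2.82 or 3.13 × 0.85 = 2.66, and power 0.951, 0.929 or 0.899. This holds the SD at 3.13 and assumes that every patient has an outcome.

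**The case against.** The best defence is that the plan is already intention-to-treat. Two of the three statements say so, including the one in the section that governs the analysis. The odd sentence sits in a quality-control section and never says that only those patients will be analysed. A reader might infer that the trial plans to drop everyone with half the course or less; the documents do not support that firmly, because the very next sentence keeps all dropouts. This part of the defence stands, and it limits the finding to a contradiction. It does not remove it: a condition for including some patients has no function unless others can be left out, and nothing marks it as belonging to a secondary analysis.

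A reader might also infer that the primary result would be biased towards real rTMS. The documents do not support that either. The 15% allowance is not tied to the first half of treatment, and patients who stop after session 10 or are lost during follow-up are untouched by the condition. Sham patients may leave for lack of effect, in which case bias can cancel or reverse.

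Finally, it would be too strong to say that the condition throws away data the trial will hold. Assessment after dropout is sought only where possible, and some patients who withdraw consent will have no post-treatment PSQI under any rule.

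**Conclusion.** The point holds as an internal contradiction about the analysis set. The more-than-half condition is incompatible with the intention-to-treat statements beside it and in the Statistical analysis section, and it carries no label that would reconcile them. If used for the primary comparison, it would exclude patients after randomisation, partly for outcome-related reasons that the article itself lists.

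The contradiction needs no assumptions. The size and direction of bias rest entirely on them. When only real-arm losses depend on outcome, the effect is small with one or two early stoppers per arm and material with four per arm and a strong link to outcome. It is absent when losses are unrelated to outcome or equally related in both arms, and it runs against real rTMS when only sham losses are related. The article does not establish a definite plan to exclude patients, or a known bias in favour of treatment.

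It should be settled before unblinding, because it decides who enters the primary comparison.

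**What to change.** Remove the more-than-half condition from the main analysis and state in its place:

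*All randomised patients are analysed in the group to which they were assigned, whatever number of sessions they received. Assessments obtained after a patient stops treatment are used. Patients who received more than half of the sessions form a supportive per-protocol set.*

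The Intervention and Quality control and guarantee sections already seek assessments from those who stop, so no new data collection is required; those assessments should be used wherever they can be obtained.

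The cost is a short change of text in the protocol, carried into the analysis plan. The estimated effect may be slightly smaller, since patients with little treatment stay in. On the figures above, power remains about 90% even if 15% of the real arm gain no more than sham, so no extra patients or visits are needed.
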